**Table 6.1.1 Drug Information**

| **Drugs** | **Specification** | **Drug storage** | **Manufacturer** |
| --- | --- | --- | --- |
| Anlotinib | 12 mg/tablet  10 mg/tablet  8 mg/tablet | Store in a sealed and dark place below 25°C | Chia Tai Tianqing Pharmaceutical Group Co., Ltd. |
| Placebo | 0 mg/tablet | Store in a sealed and dark place below 25°C | Chia Tai Tianqing Pharmaceutical Group Co., Ltd. |
| Gefitinib | 250 mg/tablet | Store at a room temperature of 15-30°C | Chia Tai Tianqing Pharmaceutical Group Co., Ltd.  Astrazeneca Pharmaceuticals Co., Ltd. |

Anlotinib and placebo are produced by Chia Tai Tianqing Pharmaceutical Group Co., Ltd., and batch numbers and expiration dates are detailed in the drug test report. Gefitinib tablets are produced by Chia Tai Tianqing Pharmaceutical Group Co., Ltd. or purchased from Astrazeneca Pharmaceuticals Co., Ltd.

- - 1. **Drug packaging**

Anlotinib is packaged in capsules, with 7 tablets per plate and 2 plates per small box.

- 1. **Dose and administration regimens**

Group A (experimental group): 250 mg gefitinib, po, qd + 12 mg anlotinib hydrochloride capsule, po, qd, D1-D14; administered under fasting conditions (taking medication at the same time every day), every 3 weeks;

Group B (control group): 250 mg gefitinib, po, qd + anlotinib hydrochloride mock capsule, 1 tablet, po, qd, D1-D14; administered under fasting conditions (taking medication at the same time every day), every 3 weeks.

Anlotinib is given at a dose of 12 mg as the initial dose (po, qd, D1-D14) every 21 days and the drug combination is used until disease progression, intolerable toxicity, withdrawal of consent, or drug discontinuation according to the investigator's judgment. If the administration is suspended due to no recovery of drug toxicity, treatment cycle is recalculated according to the regimen of consecutive 2 weeks and stop 1 week, while the follow-up period is still calculated according to the screening date. If patients discontinue anlotinib due to intolerable toxicity, gefitinib can be continued until disease progression.

**Note:** In principle, drug administration should be terminated for progressive disease (PD) patients; however, given the therapeutic characteristics of molecularly targeted drugs, the evaluation of cytotoxic chemotherapy drugs has certain defects. After the use of molecular targeted therapy in some patients, although the tumor increases, the internal tissues of the tumor may show obvious necrosis or degeneration; CT can show a decrease density within the tumor, which is generally believed that patients may benefit from the treatment. According to this protocol, for patients with obvious necrosis or degeneration of the tumor tissue and continuous improvement or stability of clinical tumor-related symptoms, if the patient voluntarily continues administration and there may be a survival benefit according to the principal investigator’s judgment, treatment can be continued until intolerable toxicity or disease progression. Close observation is required during administration.

- 1. **Drug administration, distribution, and recovery**

The study drug is governed by special personnel, and the investigator must ensure that all drugs are used only for the subjects enrolled in the study and that the dose and use are in accordance with the protocol. The remaining drugs shall be returned to Chia Tai Tianqing Pharmaceutical Group Co., Ltd., and study drugs shall not be transferred to any non-clinical participants.

The drug receipt shall be signed by two persons in duplicate, with each party (the clinical research unit and Chia Tai Tianqing Pharmaceutical Group Co., Ltd.) holding one copy. At the end of the study, the remaining drugs and empty boxes are collected, and the drug recovery sheet is signed by both parties. The distribution and collection of each drug should be recorded in a special record sheet timely.

The inspector is responsible for supervising the supply, use, storage of study drugs, and disposal of the remaining drugs.

- 1. **Destruction of study drugs**

The total quantity of study drugs shall be 120% of the design quantity, and the remaining drugs shall be returned to t Chia Tai Tianqing Pharmaceutical Group Co., Ltd. after the end of the study, which shall be recovered by the inspectors.

The investigator may destroy the used study drugs (non-state controlled chemicals) and empty boxes/bottles after written notification to the co-organizer without endangering the health of the population. The investigator should keep all study drug-handling records.

These records must document the evidence and quantity of each batch of destroyed drugs, disposal methods (as required by local law), and the person who handled the study drugs.

1. Dose Adjustment and Discontinuation
   1. **Dose adjustment of anlotinib**

The initial dose of anlotinib or placebo is 12 mg/day, and the anlotinib dose can be reduced to 10 mg/day for the first dose and 8 mg/day for the second dose. For patients unable to tolerate a dose of 8 mg/day, anlotinib should be discontinued and gefitinib should be administered alone until PD or intolerable toxicity.

|  | **Study group (anlotinib)** | **Control group (placebo)** |
| --- | --- | --- |
| Initial dose | ■■ 12 mg/day, qd | □□ 12 mg/day, qd |
| First dose reduction | ● 10 mg/day, qd | ○ 10 mg/day, qd |
| Second dose reduction | ■ 8 mg/day, qd | □ 8mg/day, qd |
| Third dose reduction | Discontinuation | Discontinuation |

- 1. **Dosage suspension and reduction**

If dosage suspension caused by drug toxicity has not recovered, the duration of dosage suspension should not exceed 6 weeks per cycle. Follow-up visits will be conducted at least every 1-2 weeks during discontinuation and the drug will be restarted at the original dose or a lower dose level after recovery of toxicity.

The subjects cannot return to the previous dosing pattern after dosage reduction and a maximum of three dose reductions are allowed in anlotinib therapy.

When patients experienced grade 3 hematological toxicities and grade 2 non-hematological toxicities, dosage suspension and reduction are considered; Dosage suspension will be performed in non-hematological toxicities including controllable nausea, vomiting, and fever with a definite cause (below 38°C) until the toxicity became tolerable. Aggressive symptomatic management without dosage suspension and reduction can also be conducted.

- - 1. **Standardization of dose suspension and reduction**

To ensure consistency of dosage adjustment, dosage suspension is performed at the time of dosage adjustments for each cycle. The criteria of dose suspension and reduction are as follows (once the criteria of dosage reduction are met which is considered poorly tolerated, a reduction should be performed).

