The incidence of HFSR decreased with increasing treatment duration in the treatment period. Discontinuing the drug if grade >2 AEs appears three times and tends to worsen, and continue drug treatment if AE resolves to normal or grade 1; If HFSR has no further occurrence, the dose of anlotinib should progressively increase until the standard dose; If grade >2 AEs reoccurs after the resumption of dosing, it is recommended to continue dosing after a dose reducing by one level; If grade 3 of AEs persists or tend to worsen, permanent discontinuation of anlotinib is recommended. Recommendations for the prevention and treatment of anlotinib-associated HFSR can be viewed in **Table 7.4.2** HFSR classification criteria (NCI-CTC AE 4.0) and recommendations for prevention and treatment.

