**Table 7.4.2. HFSR classification criteria (NCI-CTC AE 4.0) and recommendations for prevention and treatment**

| Criteria | Definition | Prevention and treatment |
| --- | --- | --- |
| Grade 1 | Minimal skin changes or dermatitis (e.g., localized erythema, hyperkeratosis, oedema, and painless), but not interfering with daily life | Continuing anlotinib administration without dose adjustment; Treating with topical medication at the first sign of symptoms. |
| Grade 2 | Significant skin changes (flaking, blisters, swelling, and hyperkeratosis) and pain, interfering with daily life and activities. | Continuing anlotinib administration with appropriate dose adjustment; Local drug; Oral B vitamins and celecoxib, and may combine with anti-inflammatory or anti-infective drugs. |
| Grade 3 | Severe skin changes (flaking, blisters, bleeding, ulcers, oedema, and hyperkeratosis) with significant pain and limited personal self-care ability. | Suspension of anlotinib; Analgesic management and topical treatment; Combination of anti-inflammatory or anti-infective drugs; Administering a lower dose of anlotinib if symptoms resolve; Discontinuing anlotinib if symptoms persist and worsen. |

1. **Proteinuria**

When grade >2 proteinuria occurs, the dose of anlotinib is interrupted and awaiting for recovering. If grade 2 or higher proteinuria occurs, continue drug treatment of anlotinib after a dose reducing by one level; if proteinuria persists and worsens, discontinue the drug.

In the event of renal insufficiency or nephrotic syndrome, the drug must be discontinued immediately and aggressive symptomatic treatment must be administered. There is no definitive treatment for proteinuria induced by anti-angiogenic inhibitors, but ACEI and ARB analogues may be administered as appropriate due to their ability in reducing intrarenal tubular pressure and thus proteinuria, as well as reduce possible cardiac AEs. Recommendations for the prevention and treatment of anlotinib-associated proteinuria can be viewed in Table 7.4.2 proteinuria classification criteria (NCI-CTC AE 4.0) and recommendations for prevention and treatment.

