**Table 7.4.3. Proteinuria classification criteria (NCI-CTC AE 4.0) and recommendations for prevention and treatment**

| Criteria | Definition | Prevention and treatment |
| --- | --- | --- |
| Grade 1 | Urokinase protein (+) or 24-hour urine protein excretion <1.0 g | Continuing anlotinib administration without dose adjustment |
| Grade 2 | Urokinase protein (++) or 24-hour urine protein excretion of 1.0-3.4 g | Continuing anlotinib administration without dose adjustment; Drug intervention should be considered; Monitor 24-hour urine routine and 24-hour urine protein excretion |
| Grade 3 | 24-hour urine protein excretion >3.4 g | Suspension of anlotinib; Consultation with a nephrologist specialist; Drug intervention should be performed; Dose reduction of anlotinib after recovery of proteinuria to ≤ grade 2; If grade 3 proteinuria still occurs after 2 dose reductions, anlotinib therapy should be permanently discontinued |

1. **Bleeding**

The PT and international normalized ratio (INR) should be closely monitored during the administration of anlotinib to monitor patients for bleeding tendencies and related symptoms; the drug should be interrupted if a grade 3-4 bleeding event occurs. If [upper gastrointestinal bleeding](https://www.sciencedirect.com/science/article/pii/S0025712508000023) occurs, anlotinib must be interrupted and aggressively treated according to clinical protocols should be performed.

1. **Thrombus**

If any arterial thrombosis (e.g., cerebral ischemia, stroke, angina, myocardial infarction) occurs, drug administration should be discontinued immediately and the study should be withdrawn. If symptomatic grade IV venous thrombosis occurs, drug administration should be discontinued in patients, with withdrawal from the study.

For patients with thrombotic symptoms, symptomatic treatment, surgery, or anticoagulant drugs should be scheduled immediately.

For patients with venous thrombosis, the criteria for dose adjustment are as follows:

| **Venous thrombosis** | **Dose adjustment** |
| --- | --- |
| Grade II | Anlotinib is maintained at the original dose level and closely monitored. |

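### Section 7.2 bars return to an earlier anlotinib dose after a reduction, section 7.4 says the dose should be raised again when hand-foot skin reaction does not recur, and nothing says which governs

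*Protocol*

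**What the plan says.** Three places in the protocol bear on the point.

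- **Section 7.2 (Dosage suspension and reduction)** sets the general rule: "The subjects cannot return to the previous dosing pattern after dosage reduction and a maximum of three dose reductions are allowed in anlotinib therapy". It names no adverse event as an exception.
- **Section 7.4, HFSR text**, deals with recurrent HFSR: interruption, resumption once the reaction has settled, and then "If HFSR has no further occurrence, the dose of anlotinib should progressively increase until the standard dose".
- **Table 7.4.2** shows how a subject comes to be below the standard dose. After grade 3 HFSR it provides for "Administering a lower dose of anlotinib if symptoms resolve". At grade 2 it continues treatment with the dose adjusted as appropriate. At grade 1 it makes no dose change.

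Section 7.1 fixes the dose steps: "the anlotinib dose can be reduced to 10 mg/day for the first dose and 8 mg/day for the second dose". Its table ends with the row "Third dose reduction | Discontinuation | Discontinuation". Section 7.4 opens by leaving management to the investigator's view of the clinical situation, with the text that follows as a reference.

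**The concern.** An instruction to raise the dose to the standard level has meaning only for a subject who is below it. Section 7.2 forbids that increase for anyone who got there by a reduction. A site that follows the HFSR text breaches 7.2, and a site that follows 7.2 departs from the HFSR text.

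This is first a patient-safety matter, because two sites could treat the same patient differently and each could cite the protocol. It also touches the data:

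- Section 6.3 makes the investigator responsible for dosing in accordance with the protocol.
- Section 5.4 lists departures from the specified dose and course among the dropout/removal criteria.
- Section 13.2 restricts the per-protocol set to subjects who met the protocol with good compliance, and refers to efficacy analysis in that set.

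Whether a re-escalated subject counts as a deviator, and possibly whether that subject stays in the per-protocol set, is therefore unsettled.

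**Working it through.** No sample-size, power or error-rate formula applies. The check is a count of dose steps, a comparison of texts, and simple proportions.

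**1. The protocol's own count of reductions.** The rows of the 7.1 table below 12 mg are 10 mg/day (first), 8 mg/day (second) and discontinuation (labelled third). That gives 3 labelled steps, the same as the maximum in 7.2. The 7.1 text agrees: "For patients unable to tolerate a dose of 8 mg/day, anlotinib should be discontinued". Table 7.4.3 agrees as well: "If grade 3 proteinuria still occurs after 2 dose reductions, anlotinib therapy should be permanently discontinued". Two reduced active levels followed by stopping is one consistent scheme.

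**2. The re-escalation rule.** Take a subject with grade 3 HFSR whose symptoms resolve.

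| Step | Source | Instruction |
|---|---|---|
| Resume after resolution | Table 7.4.2 | Lower dose |
| HFSR does not recur | 7.4, HFSR text | Dose should rise stepwise to the standard dose |
| Same subject, same time | 7.2 | No return after a reduction |

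The last two rows cannot both be met. Section 7.2 also lets a subject restart at the original or a lower dose after a suspension. That sentence concerns suspension, whereas the bar concerns what follows a reduction, so it does not resolve the conflict.

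**3. How many subjects could be touched.** The input is Table 3 in section 1.5.2.1 (12 mg, n=21, whole study process):

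- grade III HFSR: 1/21 = 4.8%
- grade I/II HFSR: 10/21 = 47.6%, not split by grade

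Assume, for illustration only, that these rates carry over to the 155 planned experimental subjects:

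- grade III: 155 × 1/21 = 7.4, about 7 subjects
- grade I/II: 155 × 10/21 = 73.8, about 74 subjects

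Neither figure estimates the number who meet the conflict. The 74 include grade 1 cases, for which Table 7.4.2 makes no dose change, and grade 2 cases whose dose may not be reduced. The 7 include any who stop for good or whose reaction recurs. Only subjects who are reduced for HFSR and then stay free of it face both rules. The table gives no rate for gefitinib plus placebo, although the same reduction steps apply to placebo under the blind.

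**The case against.** The strongest defence is that section 7.4 is reference guidance for the investigator, worded as what should be done, while 7.2 says what subjects cannot do. On that reading 7.2 prevails and there is nothing to reconcile. The first half stands: 7.4 does not order re-escalation. The second half does not follow, because no text ranks the sections. The part of 7.2 that standardises suspension and reduction also gives consistency of dose adjustment as its aim, and an unranked conflict works against that aim.

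It is also fair to say that the conflict concerns one adverse event and does not make the whole dose-modification scheme unworkable. That stands.

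A reader might infer three stronger things, which the protocol does not support:

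- **That 7.2's three reductions contradict the two reduced levels in 7.1.** They do not, because the 7.1 table itself counts discontinuation as the third reduction. At most, 7.2 is loose in calling a stop a reduction.
- **That the hold limit is impossible.** Section 7.2 says "the duration of dosage suspension should not exceed 6 weeks per cycle", while a cycle lasts 21 days. But section 6.2 recalculates the cycle after a suspension for unrecovered toxicity, so the limit can be read as applying to each hold. It is unclear whether holds accumulate, which is an ambiguity and not a contradiction.
- **That about half the experimental arm is affected, or that the PFS comparison is distorted.** The first pools grade 1 with grade 2. The protocol offers nothing from which to quantify the second.

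**Conclusion.** The contradiction is real and narrow. For a subject reduced for HFSR in whom the reaction does not recur, section 7.2 bars what the HFSR text in 7.4 says should be done, and the protocol does not say which governs. This rests on the wording alone and needs no assumption about rates.

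Its size cannot be fixed from the protocol. Grade III HFSR, the grade for which a lower dose is expressly provided, occurred in 4.8% of a sample of 21. Grade I/II occurred in 47.6%, which makes about half an upper bound. Both figures assume that phase I monotherapy experience carries over to the combination. The point deserves correction because it bears on patient safety and costs little to settle. It does not call the primary analysis into question.

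**What to change.** Reconcile section 7.2, the HFSR text in 7.4 and Table 7.4.2 into one statement on whether the anlotinib or placebo dose may be raised again after a reduction, including after a reduction for HFSR. State which section governs where the two differ. The clinical team should choose the rule; this review takes no view on which is right.

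In the same edit, tidy two wordings: say in 7.2 that the third reduction means discontinuation, as the 7.1 table already does, and say whether the 6-week hold limit applies to each hold or cumulatively.

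The cost is protocol wording and a site notification. No new procedures or data are needed. For subjects already dosed under either reading, record which rule was applied so that deviations are coded in the same way at all sites.

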**Dose Adjustment Criteria**

| **Toxicities graded by NCI** | **Hematological toxicities** |
| --- | --- |
| Grade I | Maintain the original dose (appropriate symptomatic treatment should be provided). |
| Grade II | Maintain the original dose (appropriate symptomatic treatment should be provided). |
| Grade III | Initially, suspend the drug and aggressive symptomatic treatment should be performed, and maintaining the original dose if toxicity restores to grade <II. |
| Grade IV | Initially, suspend drug and aggressive symptomatic treatment should be performed, and downward dose adjustment should be performed if toxicity restores to grade <II. |
|  | **Non-hematological toxicities** |
| Grade I | Maintain the original dose (appropriate symptomatic treatment should be provided). |
| Grade II | Symptomatic treatment and continue drug treatment should be provided. If AE resolves to grade <I within 2 weeks, continue drug treatment; If AE does not improve or aggravate, drug interruption until AE resolves to grade <I and continue drug treatment with original dose level. |
| Grade III | Drug interruption and symptomatic treatment should be provided. If AE resolves to grade <I within 2 weeks, continue drug treatment with the original dose level or at a dose reduced by one level by the investigator's discretion; Drug interruption is recommended if a grade 3 or above adverse reaction occurs. |
| Grade IV | Drug interruption and symptomatic treatment should be provided, and the dose is reduced by one level if AE resolves to grade <I; Drug interruption is recommended if a grade V AE occurs (such as Grade V kidney injury, neurotoxicity, cardiotoxicity, hepatotoxicity, and other life-threatening). |
| **AEs of special interest** | |
| Once hypertensive intracerebral hemorrhage, intracerebral hemorrhage, pulmonary hemorrhage (≥grade II), other hemorrhages (≥ grade III), arterial thrombosis, venous thrombosis (grade IV), Leukoencephalopathy syndrome, and gastrointestinal perforation occur, drug interruption is recommended and aggressive symptomatic treatment should be provided. | |

- 1. **Dose adjustment of gefitinib**

If the patient exhibits intolerable diarrhea (generally associated with dehydration), skin toxic effects, or other AEs caused by gefitinib, briefly discontinuing (up to 42 days) of gefitinib may be performed and then resuming the dose to 250 mg/day for the patient.

In the event of pulmonary symptoms (dyspnea, cough, and fever) gefitinib therapy should be interrupted, and a prompt investigation of these symptoms should occur. If interstitial lung disease is confirmed, gefitinib should be discontinued and appropriate treatment should be conducted.

No dosage adjustment is recommended for patients with different body weights, gender, ethnicity, renal function, or moderate to severe hepatic impairment due to liver metastases.

For patients treated with gefitinib combined with anlotinib who discontinue gefitinib therapy, the decision of proceeding with anlotinib is determined by the investigator.

When AEs occur, dose adjustment of gefitinib and subsequent dosing regimens are determined by the investigator.

- 1. **Management of anlotinib-related AEs**

Management of anlotinib-related AEs will be performed by the investigator based on the actual clinical situation (reference the following management).

1. **Fatigue**

Fatigue is often associated with oncologic treatment, and it is recommended to monitor the onset of severe fatigue by observation and documentation of the patient's fatigue. No dosage adjustment is necessary if grade 1-2 fatigue occurs; aggressive symptomatic treatment should be provided if grade 3-4 fatigue occurs. In absence of jaundice, thrombi, and pregnancy, progesterone drugs (such as megestrol) and multivitamins may be administered to help reduce fatigue and enhance physical performance. In addition, care must always be taken to identify other causes of fatigue such as those secondary to hypothyroidism, depression, anemia, or pain.

1. **Diarrhea**

Diarrhea may impact the digestive function, fluid and electrolyte balance of the patient, and the absorption of medications, early treatment should be performed. Diarrhea usually appears during the first few days of treatment. No dosage adjustment of anlotinib should be performed.

No dose adjustment of anlotinib should be required if grade 1-2 diarrhea occurs, and patients are recommended to: regulate dietary habits, drink more water, and eat easily digestible, absorbed, and vitamin-rich food; avoid intake of diarrhea-inducing diets (e.g., greasy, spicy foods, and coffee) or undergo medications such as stool softeners and gastrointestinal prokinetic agents; increase the diet with plenty of dietary fiber and administer micro-ecological drugs (e.g., bifid triple viable). Among them, when grade 2 diarrhea occurs, loperamide, diphenoxylate, gastric mucosal protective agents (montmorillonite powder), and berberine can be appropriately administered. Aggressive symptomatic treatment should be performed if grade 3-4 diarrhea occurs, and care must always be taken to replenish water and electrolytes to maintain fluid and electrolyte balance and provide acid-base disturbance. Immediately discontinue anlotinib until diarrhea is significantly reduced or ceases, and reduce the dose appropriate when restoring drugs.

1. **Hypertension**

Hypertension is emerging as one of the most common AEs. The [cardiovascular toxicities](https://www.sciencedirect.com/topics/medicine-and-dentistry/cardiovascular-toxicity) panel of the NCI recommends that patients with hypertension at baseline should be diagnosed before VEGF/VEGFR-inhibitor therapy, and patients should have a sustained blood pressure of <140/90 mmHg during the treatment. Blood pressure (BP) should be performed monitored before administration of the drug and especially in the first 2 weeks of treatment (daily monitoring should be performed), and monitoring must continue throughout treatment. Therefore, for patients with hypertension, the antihypertensive drugs should be administered based on individualized principles before receiving anlotinib to achieve early and favorable BP control (BP of ≤140/90 mmHg). However, prophylactic antihypertensive therapy is not recommended for patients with normal BP. Patients should be adequately informed to contact the investigator immediately for guidance when BP is >140/90 mmHg or when symptoms associated with elevated BP occur (e.g., significant headache, dizziness, visual disturbances, etc.). It has been suggested that antihypertensive drugs should be chosen according to the 2010 Chinese guidelines for the management of hypertension, regarding the risk factors for cardiovascular disease in patients. For patients combined with proteinuria, an angiotensin-converting enzyme inhibitor (ACEI) or an angiotensin receptor blocker (ARB) is recommended. A word of caution in drug selection is required that anlotinib is primarily metabolized by the lung CYP3A4 enzyme. Non-dihydropyridine calcium channel blockers (verapamil and diltiazem) can moderate CYP3A4 inhibition and are not recommended for BP control.

If a grade 3-4 increase in BP occurs, antihypertensive treatment or dose modification of this product should be performed under the guidance of the specialist. Drug discontinuation is recommended if the adverse reaction persists. This product should be permanently discontinued in patients who develop a hypertensive crisis. Recommendations for the prevention and treatment of anlotinib-associated hypertension can be viewed in **Table 7.4.1** hypertension classification criteria (NCI-CTC AE 4.0) and recommendations for prevention and treatment.

When hypertension occurs in [vital signs measurement](https://www.mdpi.com/748232), patients should rest for 15 minutes before BP is measured again. Hypertension has been identified as an AE if hypertension recurs and reaches grade II.

AEs are documented as one AE when the time interval between two hypertensive episodes is less than 1 week, and the highest grade of AE will be recorded with the time of onset defined as the time of the first hypertensive episode and the time of end defined as the time of outcome.

